## Methods

### Objective

The objective of this study was to evaluate whether EA will be an effective and safe therapy for PN caused by UTD1.

### Hypotheses

1. Electroacupuncture can improve PN symptoms caused by UTD1 compared with drug intervention. Subjective outcomes such as the evaluation scale of the European Organization for Research and Treatment of Cancer Quality of Life Questionnaire-CIPN 20-item (EORTC QLQ-CIPN20) can be improved.

2. EA can be considered a safe therapy in the treatment of advanced breast cancer. EA can improve a patient's life quality while treating PN caused by UTD1, as measured by the European Organization for Research and Treatment of Cancer Core Quality of Life Questionnaire (EORTC QLQ-C30).

### Study design

The trial is designed as a prospective, randomized, controlled, and blind study to compare the therapeutic effects of EA therapy on PN caused by UTD1. A total of 70 participants with PN caused by UTD1 will be randomly divided into two groups in a ratio of 1:1, which are namely the EA treatment group and the control group. Figure 1 shows the flowchart, which describes the research flow in detail. In addition, the trial schedule of enrolment, treatments, and outcome assessments is shown in Table 1. The reporting of this protocol is based on the SPIRIT reporting guidelines (24).

**Figure 1 F1:**
[figure not shown]
Flow chart of the study process. PN, peripheral neuropathy; UTD1, Utidelone; EA, Electroacupuncture; EORTC QLQ-CIPN20, the European Organization for Research and Treatment of Cancer, Quality of Life Questionnaire-chemotherapy-induced peripheral neuropathy 20; NCI CTCAE V5.0, National Cancer Institute Common Terminology Criteria for Adverse Events Version 5.0; EORTC QLQ-C30, the European Organization for Research and Treatment of Cancer, Quality of Life Questionnaire-Core 30.

**Table 1 T1:** Schedule of enrolment, treatments, and assessments.

**Study period**	**Screening**	**Baseline, week 0**	**Treatment period, week 1–4**	**Post-treatment, week 4**	**Follow-up, week 8**
**Enrolment**					
Eligibility screening	•				
Informed consent	•				
Random allocation	•				
Treatment			•		

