**Outcome assessment**					
(1) EORTC QLQ-CIPN20		•		•	•
(2) NCI CTCAE V5.0		•		•	•
(3) EORTC QLQ-C30		•		•	•
Safety assessment		•	•	•	•

•, Required; EORTC QLQ-CIPN20, the European Organization for Research and Treatment of Cancer, Quality of Life Questionnaire-Chemotherapy-induced peripheral neuropathy 20; NCI CTCAE V5.0, National Cancer Institute Common Terminology Criteria for Adverse Events Version 5.0; EORTC QLQ-C30, the European Organization for Research and Treatment of Cancer, Quality of Life Questionnaire-Core 30.

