### Study procedure

The duration of the trial will include three study phases, including screening in the baseline phase (week 0), 4-week treatment phase (weeks 1–4), and follow-up phase (week 8). The qualification of prospective participants will be determined by researchers who will not be involved in the assessment or treatment. At the screening meeting, patients will be given more detailed information about the study procedures. Before the first treatment (baseline, week 0), after the last treatment (post-treatment, week 4), and in the fourth week of follow-up after treatment (week 8), all participants will be required to complete several questionnaires as the outcomes of the study to evaluate the curative effect, including EORTC QLQ-CIPN20 and EORTC QLQ-C30 questionnaires. The participants cannot take drugs that may influence the outcomes of the study during the trial, including pain drugs or unspecified CIPN-related therapeutic drugs. If the patient has to take drugs that will influence the outcomes of the study due to disease progression, the patient will be considered to have dropped out. To promote enrollment, all treatment costs and outcome measurements will be free for participants.

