### Inclusion criteria and exclusion criteria

All participants will be screened according to the inclusion criteria and exclusion criteria at the baseline (Table 2 for details).

**Table 2 T2:** Inclusion criteria and exclusion criteria.

**Patients who meet the following requirements will be considered for inclusion:**	**Patients will be excluded if they have:**
(1) Diagnosed as advanced breast cancer and PN symptoms occur after using UTD1. The patient had no obvious PN symptoms before using UTD1; (2) Over 18 and under 70 years old, and the expected survival time was ≥6 months; (3) Have daily living ability and can complete all questionnaire investigation; (4) No serious heart, brain, kidney, and other diseases, KPS score >70; (5) Clear consciousness without severe mental illness or cognitive impairment; (6) Sign the written informed consent form.	(1) Diagnoses as other severe systemic diseases (e.g., cardiovascular disease, acute infectious disease, hematopathy, et al.); (2) Diagnoses as severe mental disorders, like schizophrenia; (3) PN caused by other diseases, such as diabetic peripheral neuropathy; (4) Alcohol and/or other drug abuse or dependence; (5) Pregnant and lactating women; (6) Participating in other clinical trials.

PN, peripheral neuropathy; UTD1, Utidelone; KPS, Karnofsky performance status.

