### Randomization and allocation concealment

The randomization will be performed by the Department of Scientific Research, Zhejiang Cancer Hospital. A randomization method will be used to generate the random allocation sequence of two groups in a ratio of 1:1; two groups of random serial numbers will be randomly placed in opaque, sealed envelopes by other staff who will not be involved in the study to ensure the concealment of distribution. These envelopes will be printed with consecutive numbers on the outside. The envelope with the corresponding serial number will be selected according to the participant's visit order.

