### Blinding

Participants will be informed that they have a 50% chance of being assigned to receive either of the two treatments: the EA treatment or drug treatment. However, as there is a complete difference between the treatment methods of the two groups, the participants cannot be blinded. At the same time, although acupuncture doctors also cannot achieve blindness because of the need for treatment, they will not be involved in the assessments or data analyses. The follow-up data managers who collect data and outcome assessors will be unaware of the group allocation of the participants.

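### Table 1 puts random allocation ahead of the week-0 baseline, so unblinded patients could rate their baseline CIPN20 and QLQ-C30 knowing their arm

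*Protocol article*

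**What the plan says.** Table 1 of the protocol article has five columns: Screening, Baseline (week 0), Treatment (weeks 1–4), Post-treatment (week 4) and Follow-up (week 8). The row "Random allocation" has one mark, under Screening, together with eligibility screening and informed consent. The row "1) EORTC QLQ-CIPN20" has no mark under Screening. Its first mark is under "Baseline, week 0", and the CTCAE and QLQ-C30 rows follow the same pattern.

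The text describes the timing differently. Study procedure lists the first phase as "including screening in the baseline phase (week 0", that is, screening and baseline together. The section on inclusion and exclusion criteria agrees: "All participants will be screened according to the inclusion criteria and exclusion criteria at the baseline". Study procedure ties the baseline questionnaires only to the start of treatment: "Before the first treatment (baseline, week 0".

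On allocation, the randomization section says: "The envelope with the corresponding serial number will be selected according to the participant's visit order". It does not say when the envelope is opened relative to the questionnaires, or when the patient is told the arm. Under Blinding, "the participants cannot be blinded", whereas outcome assessors are to be unaware of allocation. The Discussion describes CIPN20 as self-reported by the patient and names it as the main outcome.

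**The concern.** A baseline serves as a reference because it is measured before anyone can react to the assigned treatment. Here the comparison is open to patients (needles against tablets), and CIPN20 and QLQ-C30 are rated by those same patients. If a patient knows the arm when completing the week-0 form, hope or disappointment may affect the answers, and may do so differently in the two groups. The baseline would then be a post-randomization measurement. Change from baseline, adjustment for baseline and the table comparing the groups at entry would all inherit the difference. A later analysis plan cannot restore a pre-allocation score that was never collected.

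**Working it through.** The article gives no figure to reproduce on this point. The check is one of sequence, followed by what each possible analysis would do with a shifted baseline.

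**1. Order in Table 1.** Number the columns 1 to 5 from left to right. Random allocation is in column 1 only. CIPN20, CTCAE and QLQ-C30 are in columns 2, 4 and 5. Read literally, allocation precedes the baseline assessments.

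**2. Order in the text.** Study procedure and the eligibility section treat screening and week 0 as one phase. Within one phase the order of allocation and questionnaires is open, so either could come first. This does not match a table in which Screening is a separate, earlier column.

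**3. Does the stated anchor settle it?** Two sequences meet the requirement that baseline precede the first treatment:
- questionnaires, then envelope, then treatment;
- envelope, then questionnaires, then treatment.

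The anchor therefore does not distinguish the safe order from the unsafe one. The envelope rule does not either: visit order decides which envelope is used, not when it is opened.

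**4. Which measures are exposed.** CIPN20 and QLQ-C30 are completed by patients who cannot be blinded, so they are exposed if disclosure comes first. The CTCAE grade is set by a professional evaluator, and assessors are to be unaware of allocation, so it is less exposed.

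**5. Consequence by type of analysis.** Let *d* be the difference between arms (EA minus control) in the baseline score that is due only to knowing the arm. Let *b* be the within-arm slope of the week-4 score on baseline. The contribution of *d* to the estimated EA-minus-control difference is:
- week-4 scores alone: 0, because baseline is not used;
- change from baseline (week 4 minus week 0): −*d*;
- week-4 scores adjusted for baseline: −*b* × *d*;
- table of baseline comparability: *d* itself, appearing as an imbalance or masking one.

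If the questionnaires come first, *d* is zero by design and all four contributions vanish. The Statistical analysis section names a two-sample *t*-test or a non-parametric test and does not say whether it applies to week-4 scores or to changes. Which line applies is therefore not fixed. The article gives neither *d* nor *b*, so no numerical size can be calculated.

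**The case against.** The strongest reply is that the table may simply be drawn loosely. The text treats screening and week 0 as a single phase, no sentence says that a patient learns the arm before filling in the forms, and Figure 1, which the article says sets out the flow in detail, is not available here. That reply stands as far as it goes. A reader might infer from Table 1 that patients do rate their baseline after learning their treatment. The document does not support this, because the time of disclosure is nowhere given. The reply does not remove the problem: the table and the text disagree, and neither requires the safe order.

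A reader might also infer from the eligibility section that patients could be excluded after allocation. That does not hold together with the main point. If Table 1 governs, eligibility and consent are listed with allocation in the Screening column, ahead of baseline. If the text governs, screening and baseline are one phase and the separate earlier allocation step falls away. Late exclusion follows only by taking allocation from the table and eligibility from the text.

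Thirdly, the bias depends on how baseline is used. The named tests do not mention change or adjustment, and a comparison of week-4 scores would be untouched by the order of events at week 0. A shift that persisted unchanged to week 4 would also cancel in a change score. Both points are correct. Even so, baseline is collected for all three scales, and the first hypothesis is about improvement in symptoms, so use of baseline is a realistic prospect.

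**Conclusion.** The point holds as an inconsistency in a stated sequence, with a risk attached. Table 1 puts allocation before the self-rated baseline, the text merges screening with baseline, and nothing shown requires baseline before allocation. The schedule therefore permits an allocation-aware baseline for CIPN20 and QLQ-C30, with CTCAE less exposed.

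The consequence is conditional on two things: that the arm is disclosed before the forms are completed, and that baseline enters the analysis or is used to judge comparability. A reader might want to attach a bias in standard-deviation units. The document gives neither the shift nor the correlation that this would need, so any such figure would rest on unsourced assumptions. The correction is worth making because it is specific and nearly free; the evidence does not support calling it essential to the validity of the trial.

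**What to change.** 1. In Table 1, move the allocation mark to after the week-0 assessments, for example to a separate step between baseline and the start of treatment.
2. Make Table 1, Study procedure and the eligibility section agree on whether screening is a separate earlier step or part of week 0.
3. In Study procedure and in the randomization section, state one order: consent; eligibility confirmed; baseline CIPN20, QLQ-C30 and CTCAE completed; then the next numbered envelope opened.

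The cost is a corrected table, a few sentences and attention to the order of steps at the visit. It needs no extra assessment, no additional patients and no change to either treatment.

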**Outcome assessment**					
(1) EORTC QLQ-CIPN20		•		•	•
(2) NCI CTCAE V5.0		•		•	•
(3) EORTC QLQ-C30		•		•	•
Safety assessment		•	•	•	•

•, Required; EORTC QLQ-CIPN20, the European Organization for Research and Treatment of Cancer, Quality of Life Questionnaire-Chemotherapy-induced peripheral neuropathy 20; NCI CTCAE V5.0, National Cancer Institute Common Terminology Criteria for Adverse Events Version 5.0; EORTC QLQ-C30, the European Organization for Research and Treatment of Cancer, Quality of Life Questionnaire-Core 30.

### Ethical standards and registration

The trial will be conducted in accordance with the principles of the Declaration of Helsinki. This protocol was approved by the Medical Ethics Committee of Zhejiang Cancer Hospital on 26 July 2022 (approval number: IRB-2022-425) and registered in the Chinese Clinical Trial Registry (chictr.org.cn) with the identification number ChiCTR2200062741.

### Informed consent

All patients with PN caused by UTD1 participating in the trial will have the right to obtain all relevant information about the trial, including any benefits or potential risks, and they can participate according to their own wishes. All participants will be allowed to drop out at any point of the trial due to their wishes. The information about participants will be kept confidential. All participants need to provide written informed consent if they are included in the trial.

### Study procedure

The duration of the trial will include three study phases, including screening in the baseline phase (week 0), 4-week treatment phase (weeks 1–4), and follow-up phase (week 8). The qualification of prospective participants will be determined by researchers who will not be involved in the assessment or treatment. At the screening meeting, patients will be given more detailed information about the study procedures. Before the first treatment (baseline, week 0), after the last treatment (post-treatment, week 4), and in the fourth week of follow-up after treatment (week 8), all participants will be required to complete several questionnaires as the outcomes of the study to evaluate the curative effect, including EORTC QLQ-CIPN20 and EORTC QLQ-C30 questionnaires. The participants cannot take drugs that may influence the outcomes of the study during the trial, including pain drugs or unspecified CIPN-related therapeutic drugs. If the patient has to take drugs that will influence the outcomes of the study due to disease progression, the patient will be considered to have dropped out. To promote enrollment, all treatment costs and outcome measurements will be free for participants.

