**Methods and analysis:**

This study is a prospective randomized controlled trial. A total of 70 patients with PN caused by UTD1 will be randomly assigned to the EA treatment group and the control group in a ratio of 1:1. The patients in the EA treatment group will receive 2 Hz EA three times a week for 4 weeks. The patients in the control group will take mecobalamin (MeCbl) tablets orally, one tablet each, three times a day for 4 weeks. The main outcome measures will be the evaluation scale of peripheral neurotoxicity of chemotherapeutic drugs according to the European Organization for Research and Treatment of Cancer Quality of Life Questionnaire-CIPN 20-item (EORTC QLQ-CIPN20) and the peripheral neurotoxicity assessment rating according to NCI CTCAE version 5.0. Secondary outcomes will be the quality of life scale according to the European Organization for Research and Treatment of Cancer Core Quality of Life Questionnaire (EORTC QLQ-C30). The results will be evaluated at baseline, post-treatment phase, and follow-up. All major analyses will be based on the intention-to-treat principle.

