### Safety evaluation

All AEs during the study will be recorded, including EA-related AEs (e.g., hematoma, dizziness, and nausea) and drug-related AEs (e.g., gastrointestinal discomfort and nausea). The AEs occurrence time, treatment process, result, follow-up, and whether the participant will continue to be included in the trial will be recorded. In addition, whether the patient's cancer condition develops and quality of life will also be considered safety evaluation indicators.

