### Quality control

All acupuncture doctors and evaluators will be required to undergo special training before the trial to ensure consistent practices. The training contents will include the diagnosis of PN caused by UTD1, acupoints location, EA application technology, inclusion criteria, exclusion criteria, and evaluation criteria of case report forms. All the study data will be recorded in case report forms and entered into the electronic data capture system by independent researchers. Dropouts will be recorded throughout the trial.

This trial will be monitored by the Department of Scientific Research, Zhejiang Cancer Hospital. They will be responsible for monitoring the data and verifying the authenticity between the raw data and the recorded data to guarantee accuracy and quality throughout the study.

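### Counting patients who need outcome-influencing drugs on progression as dropouts conflicts with intention to treat unless they are still assessed and analysed as randomised; the article states neither

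*Protocol article*

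**What the plan says.** Four parts of the protocol article bear on this.

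- **Study procedure, prohibited drugs.** "The participants cannot take drugs that may influence the outcomes of the study during the trial, including pain drugs or unspecified CIPN-related therapeutic drugs".
- **Study procedure, consequence.** For someone who comes to need such a drug, the rule reads: "due to disease progression, the patient will be considered to have dropped out". The trigger is narrow: it is the need for such a drug because of progression, not progression alone.
- **Abstract, Methods and analysis.** "All major analyses will be based on the intention-to-treat principle".
- **Quality control.** "Dropouts will be recorded throughout the trial". Nothing is added about their later assessments or their place in the analysis.

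Study procedure also says of weeks 0, 4 and 8 that "all participants will be required to complete several questionnaires as the outcomes of the study". It does not say whether this still applies to someone already counted as a dropout. The Statistical analysis section names two-sample t-tests, non-parametric tests and chi-square tests, and mentions neither intention to treat nor dropouts. The Blinding section says that participants cannot be blinded.

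**The concern.** Intention to treat asks that patients be followed and analysed in the arm to which they were randomised, whatever they take afterwards. The dropout rule gives a patient who takes a certain kind of drug after randomisation the same label that the Informed consent section uses for people who leave by their own choice. If site staff read that label in its usual sense, the week-4 and week-8 questionnaires will not be collected. The tests named in the article use observed values only, so such patients would then be absent from the comparison.

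That loss is unlikely to be random. The triggering drugs include pain and neuropathy drugs, and the primary scale (EORTC QLQ-CIPN20) includes pain among its sensory items. Because participants know whether they receive electroacupuncture or tablets, recourse to other drugs could also differ by arm. At stake is whether the comparison is one of all randomised patients, as promised, or of those who did not need further drugs.

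**Working it through.** **1. The statements side by side.** The article gives no figure that depends on this rule, so there is none to reproduce. The sample size ("A total of 70 participants with PN caused by UTD1 will be randomly divided into two groups in a ratio of 1:1", 35 per group) is given without effect size, SD, power or dropout rate. The check is therefore one of consistency:

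| Question | What the article states |
|---|---|
| Is use of such a drug on progression a dropout? | Yes (Study procedure) |
| Are major analyses by intention to treat? | Yes (Abstract) |
| Do assessments continue after this kind of dropout? | Not stated |
| Do these patients stay in the analysis as randomised? | Not stated |

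The first two answers can both hold only if the last two are yes.

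**2. Size of the shift if these patients are lost.** Assumptions, none from the documents: no true effect, standard normal outcome with higher meaning worse, completers-only analysis, and removal through a latent variable that has correlation ρ with the outcome, the same in both arms.

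After the worst fraction p of an arm is removed, the mean of the rest is −ρ·φ(z₁₋ₚ)/(1−p). With ρ = 1:

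- p = 0.10: −0.1755/0.90 = −0.195
- p = 0.20: −0.2800/0.80 = −0.350
- p = 0.30: −0.3477/0.70 = −0.497

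The shift in the difference between arms, in SD, is:

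| Loss, arm A vs arm B | ρ = 1 | ρ = 0.5 |
|---|---|---|
| 20% vs 10% | 0.350 − 0.195 = 0.155 | 0.078 |
| 30% vs 10% | 0.497 − 0.195 = 0.302 | 0.151 |
| 10% vs 10% | 0 | 0 |

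The arm losing more patients has the lower mean score and so looks better.

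**3. Effect on the test.** A simulation of the two-sample t-test among completers (35 randomised per arm, two-sided 0.05, 4,000 replicates, no true effect) gave:

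| Loss | ρ | Shift (SD) | Type I error |
|---|---|---|---|
| 20% vs 10% | 0.3 | 0.051 | 5.2% |
| 20% vs 10% | 0.5 | 0.079 | 6.1% |
| 20% vs 10% | 0.7 | 0.102 | 7.6% |
| 30% vs 10% | 0.3 | 0.090 | 6.8% |
| 30% vs 10% | 0.5 | 0.152 | 8.8% |
| 30% vs 10% | 0.7 | 0.205 | 13.2% |

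The simulated shifts at ρ = 0.5 agree with the formula. With 10% lost in each arm the shift was within 0.006 SD of zero, and type I error was 4.5% to 5.7%.

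**4. Precision under equal loss.** The smallest difference detectable with 80% power at n per arm is (1.96 + 0.84)·√(2/n). At n = 35 it is 0.67 SD. Power for 0.67 SD is about 75% with 31 left per arm, 71% with 28 and 68% with 26.

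**The case against.** The strongest reply is that the article never says these patients are removed. Being considered a dropout is not exclusion from the analysis set. A dropout can be analysed as randomised with a suitable missing-data method, and a condensed article may leave that method to the full protocol or the statistical analysis plan. Study procedure also asks all participants for the questionnaires. This stands against any claim that the plan contains a completers-only analysis under an intention-to-treat label; the documents do not show that. It does not remove the point. Whether a patient is still assessed is a rule of conduct, the article states the rule that puts it in doubt, and no analysis plan can recover questionnaires that were never collected.

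Three further readings are tempting and should not be drawn:

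- **That progression data are lost**, against the Safety evaluation section, where "cancer condition develops and quality of life will also be considered safety evaluation indicators". Progression is already known when the rule applies, and dropouts are recorded. At most, follow-up after that moment is unspecified.
- **That unblinded staff apply the rule.** The Blinding section says that participants and acupuncture doctors know the allocation, and that data managers and outcome assessors do not. It does not say who declares a dropout. Only the participants' own knowledge supports the worry about uneven drug use.
- **That the false-positive rate would exceed 20%.** In the scenarios examined, this needs 30% against 10% loss, with removal wholly determined by the outcome. Nothing supports that. Follow-up is 8 weeks, and eligibility asks for expected survival of at least 6 months and KPS above 70.

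The documents also give no link between cancer progression and CIPN20 score, so that the loss is related to outcome is probable rather than shown.

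**Conclusion.** The point holds in a limited form. The dropout rule in Study procedure and the intention-to-treat statement in the abstract conflict unless two things are true that the article does not state: that outcomes are still collected from these patients, and that they are analysed as randomised.

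If they are lost, the harm depends on unequal, outcome-related loss. On the assumed rates and a moderate correlation of 0.5 it is modest: about 0.08 SD at 20% against 10%, and about 0.15 SD at 30% against 10%, with type I error of about 6% and 9%. These shifts are about double at the extreme where outcome alone decides removal. With equal loss, no true effect and the same mechanism in both arms, only precision suffers. Actual rates are unknown, so these figures illustrate the risk and do not predict it. The change is worth making because missed assessments cannot be recovered and preventing the loss costs little.

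**What to change.** Amend the dropout sentence in Study procedure to provide that such a patient:

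- is recorded as having used a non-permitted drug, with its name, the date and the reason;
- continues the scheduled CIPN20, CTCAE, QLQ-C30 and safety assessments at weeks 4 and 8;
- is analysed in the randomised arm with the values so obtained.

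State that only withdrawal of consent, loss to follow-up or death ends data collection. Report such drug use by arm. A sensitivity analysis for values obtained after the drug was started is optional, and its form can be left to the trial statistician.

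The cost is about one sentence and one case report form field; the visits are already in the schedule. The downside is that the estimate then includes the effect of the added drugs, which follows from intention to treat. The amendment does not touch which drugs are permitted or how the patient is treated.
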